
Pain catastrophising describes an adverse mental state in an individual experiencing actual or impending pain^93.^. Pain frequency is thought to play a pivotal role in catastrophizing pain. A higher frequency of pain has been shown to activate supra-spinal pathways, leading to further attention and vigilance of pain^94-96^. Some studies in breast cancer pain show a relationship between pre-surgical pain and post-surgical reported pain. It is postulated that this could stem from body hypervigilance and attention leading to somatisation and transition from acute to chronic pain^97-98^.

The precise impact of treatment side-effects (toxicity) on chronic breast pain in breast cancer survivors remains unclear, but factors are thought to include intercosto-brachial nerve damage, radiotherapy and some types of chemotherapy agents^72^. The nature of chronic breast pain may be related to the type of treatment side-effect. Surgical procedures (e.g. axillary lymph node dissection) which have a higher risk of intercosto-brachial and sensory nerve damage may lead to the development of long-term neuropathic pain, but this association remains inconclusive^98-100^. Other factors such as the presence of lymphoedema post-axillary lymph node dissection or axillary radiotherapy may also be associated^69^.

Radiation treatment in itself may be an independent risk factor in the development of long-term breast pain^78,100^, although the association may not be significant on multivariate analysis^101^. So far, no association has been shown between fractionation schedule, radiation dose, and reported pain92^,100^. Nevertheless, certain treatment combinations, such as chemotherapy followed by radiotherapy and axillary dissection may increase the risk of radiation plexopathy and thus pain^78,100^.

## 16.3 Sub-study research plan

### 16.3.1 Study objectives and design

The main objective of the REQUITE-BP sub-study is to explore the association of chronic breast pain with clinical and biological factors of breast cancer treatment, including treatment toxicity, with the aim of identifying predictive factors for chronic breast pain following surgery and radiotherapy for breast cancer.

The study has been designed as an additional sub-study to the main REQUITE study protocol.

### 16.3.2 Patient selection and recruitment

Patients taking part in the main REQUITE study at the University of Leicester will be contacted with additional pain questionnaires^64-67^ and the Pain Catastrophizing scale^68^ through post or face-to-face contact at follow-up clinics. Patients will be given/ sent a cover letter along with the additional questionnaires. They will be consented for the sub-study using one additional consent form,. If participating by post, consent forms will be countersigned on receipt.

From an original sample size of 350 treated by breast-conserving surgery and adjuvant radiotherapy, we expect a 50% return rate, yielding 175 participants. It is expected that the sample population will be representative of age, ethnicity, presence vs. absence of chemotherapy, presence vs. absence of hormonal therapies, use of painkillers, co-morbidities, and stage of disease.

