# 16.0 SUB-STUDY 4: REQUITE-BP (Breast Pain) Sub-study

## 16.1 Summary

| **TITLE** | REQUITE - Predictors of long-term breast pain after breast cancer treatment |
| --- | --- |
| **STUDY DESIGN** | A study embedded within the REQUITE main study administering pain questionnaires to a sample of breast cancer patients recruited into the main study to evaluate and better understand chronic, long-term breast pain by incorporating pain sensitivity |
| **TARGET DISEASE** | Cancer of the breast |
| **PRIMARY STUDY OBJECTIVE** | To identify clinical and biological factors that are predictive of long-term breast pain |
| **SECONDARY STUDY OBJECTIVE** | To develop a prediction model for long-term breast pain (> 2 years) after breast cancer treatment |
| **PARTICIPATING SITES** | University of Leicester |
| **STUDY POPULATION** | Breast cancer patients recruited into the main REQUITE study |
| **RECRUITMENT TARGET** | Sample size expected to be 50% of REQUITE patient cohort (n=350), approximately 175 patients. |
| **FOLLOW UP VISITS** | Single administration of questionnaires at follow-up visit or by post |
| **STUDY DURATION** | Patients to be recruited during long-term follow-up of the main REQUITE study |
| **SAMPLE COLLECTION** | Pain assessment questionnaires: Pain Sensitivity questionnaire^[[64]](#footnote-64)^, McGill pain questionnaire^[[65]](#footnote-65)^, West Haven-Yale Multi-dimensional Pain Inventory (REF) ^66^, Hospital Anxiety and Depression scale (HADs)^67^ and Pain Catastrophizing scale^68^. |
| **POWER CALCULATIONS** | We expect around 50% of the REQUITE patients to consent to enter this study, giving questionnaire data on 175 patients. In terms of genotyping, this cohort size will allow 80% power at α=0.05 to detect an Odds Ratio >1.42 given realistic parameters (prevalence 0.44, allele frequency 0.2, D’ 0.8) |

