## 16.2 Background

### 16.2.1 Chronic breast-pain following breast cancer treatment

Breast cancer is the most frequently diagnosed cancer in women^69^. The prevalence of chronic pain in breast cancer patients ranges from 25-60% within different populations, but it tends to be underreported by survivors^69^. Research has shown that chronic pain has an association with reduction in quality of life, affecting work re-entry, productivity and an individual’s identity^71,72^

Patients regard the risk of long-term breast pain as an important factor in treatment decision-making^73^. Owing to improvements in diagnosis and treatment, there are an increasing number of long-term breast cancer survivors living with late side-effects of treatment such as chronic breast-pain^71,74^. The causes associated with certain types of pain after breast cancer treatment have been clearly identified, for example, peripheral neuropathy associated with chemotherapy, or bone pain with aromatase inhibitors^75,76^. However, the underlying causes and mechanism of long-term breast pain in breast cancer survivors remain unclear.

Studies of breast cancer survivors have shown that chronic breast pain generally resolves with time^72,77,78^. Nevertheless, these studies have not considered other factors, such as ethnicity and age. In terms of ethnicity, studies in different clinical chronic-pain conditions have shown that pain perception can vary owing to differences in sociocultural and neurobiological processes^79-84^. In older patients, the increased incidence in chronic breast pain has been attributed to the more aggressive nature of cancer, use of chemotherapy and links to anxiety and depression^85,86^. Our understanding of the interaction between the protective effect of time and other patient clinical or biological factors is limited.

Pain perception is subjective, with many neurocognitive aspects modulating the end pain experience87. Anxiety has been linked with the emotional response to pain, however, the exact effect of anxiety on pain perception remains ambiguous^88-90^. Within breast cancer survivors, patients with anxiety and depression are more likely to report long-term pain post-breast cancer treatment with a higher percentage being younger women^70,91,92^.

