### 16.3.3 Study methodology and data analysis

In order to assess patients’ perspective of chronic breast pain we will administer and collect questionnaire data on pain and pain sensitivity either face-to-face in the clinic or by post. We will include five questionnaires (Pain Sensitivity questionnaire^64^, McGill pain questionnaire^65^, West Haven-Yale Multi-dimensional Pain Inventory (REF)^66^, Hospital Anxiety and Depression Scale (HADS)^67^, and the Pain Catastrophizing scale^68^. The inclusion of the Pain Sensitivity^64^ questionnaires is to collect data to account for confounders of pain perception that are not already present in the REQUITE data.

Pain questionnaires will be sent out with a cover letter, consent form and patient information sheet attached. Postal questionnaires will have a pre-paid envelope enclosed to return questionnaires and the consent form. Each questionnaire will be identified using the patient’s unique REQUITE ID so data can be matched with the REQUITE database, but all other aspects are anonymised.

We will investigate the association of long-term breast pain at 2 years recorded in the main study using the EORCTQLQ-C30 and –BR23^102^ tools by integrating the additional questionnaire data with predictive variables from the REQUITE database, including but not limited to treatment details, co-morbidities, toxicity and other PROMs data using multivariate statistical analysis. Whole genome SNP data will be also be incorporated.

^102^ Sprangers MAG, Groenvold M, Arraras JI, et al.. The European Organisation for Research and Treatment of Cancer: Breast Cancer Specific Quality of Life Questionnaire Module: First results from a three-country field study. J. Clin. Oncol

14:2756-2768, 1996.

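### REQUITE-BP rests on the half of patients expected to return pain questionnaires; if return depends on pain, the prediction model's baseline risk is wrong, and 24-month pain data scheduled for all breast patients go unused

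*Protocol*

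**What the plan says.** REQUITE-BP (Protocol section 16) is run at Leicester alone. Section 16.3.2 sets the source sample, "From an original sample size of 350 treated by breast-conserving surgery and adjuvant radiotherapy", and adds that "we expect a 50% return rate, yielding 175 participants". The summary in 16.1 places enrolment in long-term follow-up, with the questionnaires given once, in clinic or by post. The five instruments cover pain sensitivity, pain, anxiety and depression (HADS) and catastrophizing. The secondary objective is "To develop a prediction model for long-term breast pain (> 2 years) after breast cancer treatment".

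Section 16.3.3 takes the outcome from the main study, as breast pain at 2 years on C30 and BR23. The analysis proceeds "by integrating the additional questionnaire data with predictive variables from the REQUITE database", with whole-genome SNP data added and the method given only as multivariate. The power statement in 16.1 counts "giving questionnaire data on 175 patients" and applies that number to genotyping as well: "this cohort size will allow 80% power at α=0.05 to detect an Odds Ratio >1.42", with "prevalence 0.44, allele frequency 0.2".

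On who replies, 16.3.2 expects the sample to represent age, ethnicity, chemotherapy, hormonal therapy, painkiller use, co-morbidities and stage. The 24-month pain outcome is not named. Section 12.1 schedules C30 and BR23 at 24 months for every breast patient, and section 6.2 collects the DNA sample (Sample A) from all patients. Returned forms carry the REQUITE identifier so that they can be matched to the main database.

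**The concern.** About half of the eligible patients are expected to select themselves into a pain survey at a time when most will already know whether they have lasting breast pain. Someone in pain may be more inclined to answer five questionnaires about it, or less. Either way, the share with pain among responders would differ from the share among patients treated, and a prediction model takes its baseline risk from that share.

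Mood could matter too. Section 16.2.1 notes that "patients with anxiety and depression are more likely to report long-term pain post-breast cancer treatment", so reply might depend on both the outcome and the traits measured by HADS and the Pain Catastrophizing scale.

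The protocol has the means to look at this, because the outcome is scheduled whether or not a patient replies. Section 16.3.3 makes no use of it. It plans no comparison of responders with non-responders, no weighting, and no analysis that includes non-responders. Clinical and SNP predictors need no questionnaire at all, yet the power for genotyping is also computed on the 175.

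**Working it through.** **Inputs.** From the protocol: 350 approached and 50% return (16.3.2); pain prevalence 0.44 (16.1); chronic pain 25–60% across populations (16.2.1); 2-year data expected for 75% of enrolled patients, stated for toxicity data (7.1). Assumed: the difference d in response between patients with and without pain, since the protocol gives none.

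**The plan's own figure.** 350 × 0.50 = 175. It reproduces.

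**Baseline risk.** Hold overall response at 0.50. Response without pain is 0.50 − 0.44d and response with pain is that plus d. Prevalence among responders is 0.44 × (response with pain) / 0.50, and the log-odds intercept shifts by ln(response with pain / response without pain).

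| d | with pain | without pain | prevalence among responders | intercept shift |
|---|---|---|---|---|
| −0.20 | 0.388 | 0.588 | 0.34 | −0.42 |
| −0.10 | 0.444 | 0.544 | 0.39 | −0.20 |
| 0 | 0.500 | 0.500 | 0.44 | 0 |
| +0.10 | 0.556 | 0.456 | 0.49 | +0.20 |
| +0.20 | 0.612 | 0.412 | 0.54 | +0.40 |

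At the ends of this range the average predicted risk is off by a factor of 0.388/0.50 = 0.78 or 0.612/0.50 = 1.22. For scale, the 95% sampling half-width at n = 175 is 1.96 × √(0.44 × 0.56/175) = 0.07. A 20-point difference goes beyond that; a 10-point difference does not. With true prevalence 0.25, differences of −20 and +20 points give 0.175 and 0.325; with 0.60 they give 0.50 and 0.70.

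**Odds ratios.** Let r(x,y) be the response probability for factor x and pain y (1 = present, 0 = absent). Then observed OR = true OR × [r(1,1) × r(0,0)] / [r(1,0) × r(0,1)]. Illustrative patterns:

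- Reply depends on pain only (0.60 with, 0.42 without): (0.60 × 0.42)/(0.42 × 0.60) = 1. No bias.
- Reply depends on both, multiplicatively (r(0,0) = 0.48, r(0,1) = 0.60, r(1,0) = 0.36, r(1,1) = 0.45): 0.216/0.216 = 1. No bias.
- Either one raises reply and having both adds nothing (0.40 in the r(0,0) cell, 0.60 elsewhere): 0.24/0.36 = 0.67, so a true OR of 2.0 appears as 1.33.
- The two together raise reply strongly (0.45, 0.50, 0.45, 0.70 in the same cell order): 0.315/0.225 = 1.4, so 2.0 appears as 2.8.

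Both direction and size follow from the chosen pattern, and the protocol supports none of them over the others.

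**Outcome data available.** If the 75% applies to the C30/BR23 forms, 0.75 × 350 = 262.5, about 263 patients, against 175.

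**The case against.** The strongest reply is that nothing in the protocol shows reply to depend on pain. A reader might infer that responders will be enriched for pain and that the model over-predicts. The documents do not support that: no response rate by pain or mood is given, and under-prediction is equally open. This stands, so the point is a risk and not an established error.

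A reader might also infer that odds ratios for anxiety and catastrophizing are biased whenever pain and mood both affect reply. That is not a general rule, as the multiplicative case shows. Nor can the OR of 1.42 be used to size such a bias, because 16.1 states it for genotyping.

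A third tempting reading is that the main study already holds the outcome for all non-responders. Section 12.1 only schedules the forms, the 75% in 7.1 refers to toxicity data, and non-responders may be the same patients whose 24-month forms are missing.

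The representativeness list is also not empty on this subject. Painkiller use is a partial proxy for pain, and co-morbidities may include mood, since 14.3.2 and 15.3.2 give anxiety/depression as an example of that term. The claim is therefore limited to the pain outcome not being named.

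Finally, no responder-only rule is written down, and response weighting is often left to an analysis plan. Both are fair. But the protocol itself fixes the self-selected sample, the 175, the outcome and the merge, and relies on an expectation of representativeness that leaves out a variable the main study is scheduled to record.

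**Conclusion.** The point holds as a conditional risk with a cheap remedy. The design in 16.1, 16.3.2 and 16.3.3 rests the analysis and the genotyping power on about 175 of 350 patients, who choose to reply normally after the 24-month outcome is recorded. If reply depends on pain beyond what the model's predictors explain, the baseline risk is wrong. Under assumed response differences of −20 to +20 points, prevalence 0.44 appears as 0.34 to 0.54; with no dependence there is no shift. Odds ratios for psychological factors are at risk only under joint, non-multiplicative dependence, and the size of that bias cannot be derived from the protocol.

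Two timing matters limit what the model can claim. HADS and catastrophizing are measured once, normally at or after the outcome, so pain may have changed the scores whatever the response rate. And 16.1 speaks of pain beyond 2 years while 16.3.3 uses pain at 2 years; these should be reconciled.

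**What to change.** Amend 16.3.3 as follows:

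- (a) Compare responders with all approached patients on the available 24-month C30/BR23 pain scores and on baseline main-study data.
- (b) Fit clinical and SNP predictors in all Leicester breast patients with a recorded 24-month outcome, subject to main-study consent covering this use.
- (c) For models that use the questionnaire scores, apply inverse-probability-of-response weights that include 24-month pain and main-study quality-of-life scores, and show the unweighted fit alongside.
- (d) Set the prediction model's intercept so that average predicted risk matches the pain prevalence among all approached patients with a recorded outcome.
- (e) Report HADS and catastrophizing results as associations.

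The cost is a few sentences, a check of consent and a modest amount of extra analysis on data the main study already schedules. Weighting will widen the intervals somewhat. Correction is only partial where reply depends on mood that the main study does not record, or where 24-month data are missing.

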### 16.3.3 Study methodology and data analysis

In order to assess patients’ perspective of chronic breast pain we will administer and collect questionnaire data on pain and pain sensitivity either face-to-face in the clinic or by post. We will include five questionnaires (Pain Sensitivity questionnaire^64^, McGill pain questionnaire^65^, West Haven-Yale Multi-dimensional Pain Inventory (REF)^66^, Hospital Anxiety and Depression Scale (HADS)^67^, and the Pain Catastrophizing scale^68^. The inclusion of the Pain Sensitivity^64^ questionnaires is to collect data to account for confounders of pain perception that are not already present in the REQUITE data.

Pain questionnaires will be sent out with a cover letter, consent form and patient information sheet attached. Postal questionnaires will have a pre-paid envelope enclosed to return questionnaires and the consent form. Each questionnaire will be identified using the patient’s unique REQUITE ID so data can be matched with the REQUITE database, but all other aspects are anonymised.

We will investigate the association of long-term breast pain at 2 years recorded in the main study using the EORCTQLQ-C30 and –BR23^102^ tools by integrating the additional questionnaire data with predictive variables from the REQUITE database, including but not limited to treatment details, co-morbidities, toxicity and other PROMs data using multivariate statistical analysis. Whole genome SNP data will be also be incorporated.

^102^ Sprangers MAG, Groenvold M, Arraras JI, et al.. The European Organisation for Research and Treatment of Cancer: Breast Cancer Specific Quality of Life Questionnaire Module: First results from a three-country field study. J. Clin. Oncol

14:2756-2768, 1996.

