**Genotyping**

It is estimated that 2-year toxicity data (1-year for lung) will be available for 75% of enrolled patients. Based on effect sizes observed for genetic associations with radiation toxicity, a power calculation for the genetic assays shows that 1,575 patients for breast and prostate cancer each has 80% power to detect a RR of >1.56 for at least grade 2 toxicity (α = 5 x 10^-5^ for 1000 SNPs, allele freq = 0.25, toxicity rate = 20%), or with more stringent criteria a 90% power to detect a RR >1.66 (α = 1 x 10^-5^, allele freq = 0.25, toxicity rate = 20%). For 825 patients with lung cancer the detectable RR would be 1.78 and 1.92.

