## 7.2 Statistical Data Analysis

In a first stage the data from the REQUITE multi-centre observational study will be used to validate published statistical models that use clinical and biomarker data to predict a patient’s risk of long-term side-effects following radiotherapy in patients with prostate, breast or lung cancer. Variables considered will be dose-volume data of organs and tissues at risk, dose fractions and overall treatment time, patient-related cofactors (e.g. age, weight, diabetes, and smoking), use of concurrent treatment (e.g. chemotherapy) and genotyping data. If necessary, individual clinical toxicity endpoints will be combined to derive tissue, organ or overall radiosensitivity measures (e.g. by STAT score or principal component analysis). Validation of risk factors will involve univariate analysis with Bonferroni correction and multivariate analysis. The strength of association of predictors will be assessed by calculation of the odds ratios.

Nomograms, logistic regression-, ordinal logistic regression-, and NTCP (normal tissue complication probability) models published in the literature will be considered for the prediction model validation. Validation of the prediction models in the REQUITE cohort will be evaluated by: (a) Calibration: assessing the agreement between observed and predicted probabilities using the Hosmer-Lemeshow “goodness-of-fit” test. (b) Discrimination: assessing the ability of the models to discriminate between those with and those without toxicity. For binary endpoints the area under the receiver operating curve (ROC) will be used with derivation of sensitivity and specificity for a chosen probability threshold. For polychotomous endpoints c-statistic will be used as rank order statistic. (c) Clinical usefulness: the “net benefit” (NB) will be calculated (NB=(TP−wFP)/N, where TP is the number of true-positive classifications, FP the number of false-positive classifications). w is a weight equal to the “ratio of harm to benefit” (w=cutoff/(1−cutoff), where cutoff is the probability threshold which is chosen to define the treatment rule (e.g.: the level of non-acceptable toxicity)). A clinically useful model should have an NB>cut-off.

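### The breast-pain sub-study's stated power (80% for OR above 1.42 at alpha 0.05) is a single-variant figure that does not apply to the whole-genome SNP analysis it announces, and it does not reproduce even for one variant

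*Protocol*

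**What the plan says.** The power row of section 16.1 (Summary of REQUITE-BP) reads: "In terms of genotyping, this cohort size will allow 80% power at α=0.05 to detect an Odds Ratio >1.42 given realistic parameters", the parameters being "prevalence 0.44, allele frequency 0.2, D’ 0.8". It gives one prevalence, one allele frequency and one D'. Section 16 names no variant and gives no number of variants. The cohort size is in section 16.3.2: "we expect a 50% return rate, yielding 175 participants", from 350 patients.

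Section 16.3.3 describes a multivariate analysis of breast pain at 2 years and adds: "Whole genome SNP data will be also be incorporated". It gives no SNP count, candidate list, score, significance level or exploratory label.

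For the main study, section 7.1 (Genotyping) uses "α = 5 x 10^-5^ for 1000 SNPs, allele freq = 0.25, toxicity rate = 20" (the last figure is a percentage), with "α = 1 x 10^-5^, allele freq = 0.25, toxicity rate = 20" as the stricter option. Section 7.2 adds: "Validation of risk factors will involve univariate analysis with Bonferroni correction and multivariate analysis". Section 6.6.1 says that, if whole-genome data are collected, the chosen markers will be extracted from them and the full data analysed separately for association.

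**The concern.** A power statement has to use the significance level of the analysis it supports. The one in 16.1 fits a single pre-chosen variant tested at 0.05. The analysis in 16.3.3 draws on whole-genome data, for which the programme's own practice in 7.1 implies a far smaller alpha. The two sections cannot both describe the same analysis.

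The primary objective of REQUITE-BP is to find clinical and biological factors that predict long-term breast pain, and the secondary objective is a prediction model. Anyone judging whether 175 patients can meet the genetic part of these aims has only the figure in 16.1. If that figure is wrong for the planned analysis, a null genetic result would be over-interpreted, and the sub-study would look able to detect effects that it cannot.

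**Working it through.** **Inputs.** From the protocol: N = 175 (16.1, 16.3.2); pain prevalence 0.44, allele frequency 0.2, D' 0.8, alpha 0.05, power 80% (16.1); main-study alpha 5 x 10^-5 for 1000 SNPs (7.1). Assumed: a two-sided test, since sidedness is not stated. The number of SNPs is not given, so 100,000 to 1,000,000 is taken as a range.

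**Main-study level.** 0.05 / 1000 = 5 x 10^-5, so the level in 7.1 is a Bonferroni level. The same rule gives 5 x 10^-7 for 100,000 tests and 5 x 10^-8 for 1,000,000.

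**Allelic test.** Cases: 0.44 x 175 = 77 patients, 154 alleles. Controls: 98 patients, 196 alleles. With allele frequencies q1 (cases) and q0 (controls) and pooled frequency q:

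- SE0 = sqrt[q(1 − q)(1/154 + 1/196)]
- SE1 = sqrt[q1(1 − q1)/154 + q0(1 − q0)/196]
- power = Φ{[(q1 − q0) − z × SE0] / SE1}, where z is the upper alpha/2 normal quantile

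The protocol does not say whether 0.2 is the frequency in all patients or in controls, so both were run.

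*0.2 in all patients, OR 1.42:* q1 = 0.2316, q0 = 0.1751, difference 0.0565, SE0 = 0.0431, SE1 = 0.0435.
- At 0.05: Φ[(0.0565 − 1.960 x 0.0431)/0.0435] = Φ(−0.64) = 26%.
- At 5 x 10^-5: Φ[(0.0565 − 4.056 x 0.0431)/0.0435] = Φ(−2.72) = 0.33%.

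*0.2 in controls, OR 1.42:* q1 = 0.2620, q0 = 0.2000, difference 0.0620, SE0 = 0.0451, SE1 = 0.0455.
- At 0.05: Φ(−0.58) = 28%.
- At 5 x 10^-5: Φ(−2.66) = 0.39%.

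Solving for the OR with 80% power:

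| Alpha | Power at OR 1.42 | Detectable OR, 0.2 in controls | Detectable OR, 0.2 overall |
| --- | --- | --- | --- |
| 0.05 | 26–28% | 1.99 | 2.13 |
| 5 x 10^-5 | 0.33–0.39% | 3.18 | 3.90 |
| 5 x 10^-7 | under 0.02% | 3.94 | 5.33 |
| 5 x 10^-8 | under 0.01% | 4.33 | 6.18 |

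These figures ignore D'. An additive logistic model (0.2 overall) gives detectable ORs of 2.16, 4.27 and 7.53 at 0.05, 5 x 10^-5 and 5 x 10^-8. Taking D' 0.8 as a 0.8 attenuation raises them to 2.67, 6.98 and 17.4.

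**Can the plan's 1.42 be reproduced?** Not as an odds ratio in 175 patients. A one-sided additive test has 37% power at 1.42 and a detectable OR of 1.97. A two-sided additive test would need about 806 patients for 80% power at OR 1.42, or about 1,259 with D' 0.8. The figure comes close only if 1.42 is a multiplicative genotype relative risk, either one-sided with D' ignored (81.9% power) or with 175 cases plus 175 controls, two-sided with D' 0.8 (82.8%). The protocol states an odds ratio and 175 patients in all. On the relative-risk reading with 175 patients, power at 5 x 10^-5 is still at most 9.7%.

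**If 0.05 were applied to a whole panel.** Expected false associations under the null = number of SNPs x 0.05: 50 for 1,000, 5,000 for 100,000 and 50,000 for 1,000,000.

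**The case against.** A reader might infer that the sub-study will declare every SNP with p below 0.05 associated with pain, so that thousands of false variants enter the prediction model. The protocol does not support that. The 0.05 appears only as an input to the power calculation in 16.1, and no section makes it a decision rule or a rule for model entry. The word used in 16.3.3 is compatible with a few chosen markers or a score as well as a scan. The SNP count is not given, so any false-positive total rests on an assumption. Nor do 0.05 for one variant and 5 x 10^-5 for 1000 SNPs conflict in themselves, since both hold the same familywise level.

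It can also be said that sections 6.6.1 and 7.2 show sensible handling (chosen markers extracted, separate association analysis, Bonferroni correction), and that a threshold may properly be left to an analysis plan not shown here. This stands in part. Section 16.3.3 does not import those provisions, whereas section 13.3.3 expressly adopts the main-study analysis for sub-study 1, so carry-over is arguable. If the correction does carry over, false positives are controlled but the 80% power claim fails. An analysis plan can set a threshold, but it cannot make the protocol's power figure true.

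Restricting the genetics to one named variant or one score would be a design preference. The inconsistency does not require it.

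**Conclusion.** The power statement in 16.1 does not apply to the genetic analysis announced in 16.3.3. At the main study's own level of 5 x 10^-5, 175 patients have below 0.4% power for OR 1.42. They can detect, with 80% power, ORs of about 3.2 to 3.9 at that level and about 4.3 to 6.2 at 5 x 10^-8. These values assume a two-sided allelic test with the causal SNP typed, and they are larger with D' 0.8 or an additive model.

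Multiplicity is only part of the shortfall. For a single variant at 0.05 the power is about 26% to 28% and the detectable OR about 2.0 to 2.1, so 1.42 fails on its own terms as an odds ratio.

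The 5,000 to 50,000 false associations are conditional: they would be expected only if 0.05 were applied unadjusted to 100,000 to 1,000,000 SNPs, which the protocol does not say. The point should be corrected, but it does not show that the planned analysis is invalid.

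**What to change.** - **Section 16.1:** replace the power statement with the OR detectable at the multiplicity-adjusted alpha for the number of variants to be tested. State sidedness, genetic model, what the allele frequency refers to and how D' enters. If one pre-specified variant or score is meant, say so, name it and give the correct effect at 0.05.
- **Section 16.3.3:** state what the whole-genome data will be used for. Label any scan exploratory and judge it at a genome-wide corrected level, in line with 7.1 and 7.2, so that SNPs are not selected on unadjusted p below 0.05.

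This is a change of wording and needs no further patients or data. The cost is a less favourable stated detectable effect.
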